## Professional Summary

Preterm birth, defined as birth before 37 weeks' completed gestation, is a major challenge facing modern obstetrics, with a global prevalence of 9.6% and over a million annual neonatal deaths. The authors of the 2012 WHO report 'Born Too Soon: The Global Action Report on Preterm Birth, highlighted the unacceptably high and seemingly irretractable rate of prematurity worldwide, and emphasised the importance of continued research into biomarker strategies to predict women at risk and target clinical management appropriately as well as research into optimal interventions to reduce the risk of preterm birth.

In clinical practice, once a woman has been identified as being at risk of spontaneous preterm birth (sPTB), as defined by a short cervical length (<25 mm) on transvaginal ultrasound scan, a decision regarding prophylactic treatment must be made. There are three interventions with the potential to improve outcome in these high-risk women prior to 24 weeks' gestation: cervical cerclage (stitch), vaginal progesterone treatment and cervical pessary. Each have been shown to have similar benefit in reduction of sPTB in women who develop a short cervix, but there have been *no* randomised control trials (RCTs) to compare the efficacy of each intervention; decision for intervention is currently based upon clinician experience and patient preference. This trial will evaluate whether a cervical cerclage, cervical pessary or vaginal progesterone are equally efficacious to prevent premature birth for women at high-risk of preterm birth who develop a short cervix (<25 mm) between 14+0 and 23+6 weeks' gestation as measured by transvaginal ultrasonography.

It will evaluate the impact of the three interventions on:

1. Obstetric outcome –premature birth rate <37 weeks' of gestation (primary), 34 weeks and 30 weeks (secondary outcomes).
2. Short-term neonatal outcomes –a composite of death and major morbidity

It will also explore whether success of the intervention can be predicted by pre-intervention biomarker and status (cervicovaginal fluid, blood and saliva).

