### 1.4 Rationale for pre-intervention predictive biomarker testing in parallel

Whilst sPTB culminates in a common pathway of myometrial activation, cervical dilation and rupture of membranes, it is initiated by a number of different factors, which hinders accurate identification of at risk women and application of a 'one size fits all' preventative intervention. It is anticipated that the multiple pathways and pathologies preceding cervical shortening and sPTB, and thus a woman's response to various preventative interventions, may be differentiated by the expression of different biomarkers. We predict that the observed intervention effects may be enhanced by selection of sub-groups of women according to their biomarker expression i.e. that the underlying pathophysiology may determine the success of one intervention over the other. 'Pre-intervention' samples of blood, saliva and CVF will be taken from all women when randomised, and two weekly thereafter until 24 weeks' (or delivery). Biomarkers measured will include fFN, natural antimicrobial peptides and other inflammation related markers and salivary progesterone, whilst creating a biobank of samples for future analysis of other potential candidate biomarkers. We will also analyse blood biomarkers and DNA extracted from whole blood for genetic differences (e.g. SNP polymorphisms) in women destined to deliver prematurely during pregnancy compared to those who deliver at term. Bacterial and viral DNA/RNA extracted from vaginal swabs to determine the relationship between candidate biomarkers the vaginal microbiome and response to intervention. ≥

[figure not shown]

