### **2.2 Objectives**

The primary objectives of this study are:

- To determine if treatment with cervical cerclage, cervical pessary or vaginal progesterone in women at high risk of preterm birth who develop a short cervix by ultrasound measurement are equally efficacious to improve obstetric outcome by lengthening pregnancy and reducing the incidence of preterm delivery before 34 weeks' gestation.
- To evaluate the impact of the interventions on short term neonatal outcomes, assessed as a composite of perinatal death (within 28 days) and major morbidity

The secondary objectives are:

- To undertake an exploratory analysis to determine whether the response to intervention for a short cervix is related to the pre-intervention biomarker status (CVF, blood, saliva)
- To evaluate the acceptability to women and clinicians of each of the three treatment arms
- To assess the impact of both management strategies on health economic outcomes for mother and infant in terms of number of nights in each hospital setting; cost data to hospital discharge/28 days post natal (it is anticipated that a 6 month and 2 year follow up may be performed if funding is obtained).

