## 5 Sample size, power and statistical analysis

Our previous experience (captured by a robust database of outcome data from >2000 women attending our prematurity clinic) indicates that approximately 50% of women with short cervixes (<25 mm) treated with cerclage deliver early <37 weeks. From existing published evidence, we have good reason to believe that cerclage, vaginal progesterone and silicone pessary are all of approximately equal efficacy and reduce the rate of prematurity in women from 75% (untreated) to around 50% [6,8,9,15]. We therefore determine to confirm this by a 3-arm equivalence study. Equivalence is defined as agreement to within 20% (e.g. 40% to 60%). Following Jones *et al* (1996), we allow for differences in both directions in calculating the power. Complete data on 170 women per arm (510 in all) will give us 90% power to detect difference clinically important differences of 20% or more in either direction. To allow for dropouts, we aim to recruit 540 women in total.

Analysis will be according to intention to treat. The main outcome is delivery before 37 weeks'. Results will be presented as both odds ratios and risk differences, leading to number needed to treat (NNT) if appropriate, according to CONSORT guidelines. Given that high risk women with a history of invasive cervical surgery, and those with incidental findings of a short cervix may have a different pathophysiology to those women with a history of preterm birth, sub-group analysis will be performed according to risk factor. As we are powering for equivalence in the maternal outcome, it is not anticipated that the neonatal outcomes will be different however we will collect data on composite neonatal end point (not specifically powered for equivalence).

For biomarker analysis, results will be analysed at each time point in a cross sectional analysis, and on a case-control basis. We will express the overall usefulness of each marker for prediction of the primary outcome as a ROC area (Receiver Operating Characteristic), with 95% confidence interval and p-value. We will describe the performance of the most useful markers in terms of sensitivity, specificity and related measures for selected cut-points. We will use logistic regression in order to identify possible useful combinations of markers; where possible, we will use the repeated measurements to describe the change in test performance with gestation.

[figure not shown]

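### The biomarker objective asks whether marker status modifies response to the randomised treatments, but the analysis in Section 5 is prognostic only and makes no use of the treatment arm

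*Protocol*

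**What the plan says.** **The question.** Protocol Section 2.2 lists, among the secondary objectives and as an exploratory analysis, to "determine whether the response to intervention for a short cervix is related to the pre-intervention biomarker status". The Professional Summary puts it as to "explore whether success of the intervention can be predicted by pre-intervention biomarker and status". Section 1.4 gives the reasoning: the investigators predict that "the observed intervention effects may be enhanced by selection of sub-groups of women according to their biomarker expression", and that "the underlying pathophysiology may determine the success of one intervention over the other".

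**The analysis.** The biomarker paragraph of Section 5 plans a cross-sectional analysis at each time point and a case-control comparison. It continues: "We will express the overall usefulness of each marker for prediction of the primary outcome as a ROC area". It then promises the "performance of the most useful markers in terms of sensitivity, specificity and related measures for selected cut-points", logistic regression for the stated purpose of finding useful marker combinations, and use of the repeated samples to describe how test performance changes with gestation.

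**Related statements.** The only subgroup analysis in Section 5 is by clinical risk factor, on the ground that pathophysiology may differ. Section 2.4.2 (ix) adds that biochemical results will be correlated with maternal and fetal outcomes. Section 3.5 makes sampling optional and dependent on site facilities.

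**The concern.** Section 1.4 describes effect modification: the difference between treatments may depend on a marker measured before treatment. Only a comparison of randomised arms across marker levels can show that. Each step listed in Section 5 instead relates a marker, or a combination of markers, to delivery before 37 weeks without reference to arm. That measures prognosis.

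The two properties are separate. A marker can predict preterm birth well and give no help in choosing between cerclage, pessary and progesterone. Another can show no overall association and still indicate which treatment does better. If markers are ranked by ROC area and the best are taken forward, the first kind is promoted and the second dropped. The trial would hold randomised data suited to the question and not use them for it. An interaction analysis added only after the results are seen would also be open to the charge of being post hoc.

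**Working it through.** **1. The plan's own figure.** Section 5 gives no figure for the biomarker analysis. Its only power figure is 90% for equivalence within 20 points at 170 women per arm and a 50% event rate. Alpha is not stated; one-sided 0.025 is assumed here.

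- SE = √(2 × 0.5 × 0.5 / 170) = 0.0542.
- Power = 2Φ(0.20/0.0542 − 1.96) − 1 = 91.6%, close to the stated 90%.

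The figure reproduces, so 170 per arm and a 50% event rate are used below.

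**2. Can a ROC area tell prognosis from differential response?** Take a binary marker with 50% prevalence (assumed), equal arms and an overall event rate of 50%. For a binary marker, ROC area = (sensitivity + specificity)/2. With 50% prevalence and a 50% event rate, sensitivity equals the event rate in marker-positive women, and specificity equals one minus the rate in marker-negative women. All rates below are illustrative, and arms are pooled.

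| Marker | Event rate, positive/negative, by arm (%) | Pooled rate, positive/negative (%) | Pooled ROC area | ROC area by arm |
|---|---|---|---|---|
| Prognostic only | 65/35, 65/35, 65/35 | 65/35 | 0.65 | 0.65, 0.65, 0.65 |
| Strong effect modifier | 80/20, 65/35, 50/50 | 65/35 | 0.65 | 0.80, 0.65, 0.50 |
| Opposite effects in two arms | 70/30, 30/70, 50/50 | 50/50 | 0.50 | 0.70, 0.30, 0.50 |
| No association | 50/50, 50/50, 50/50 | 50/50 | 0.50 | 0.50, 0.50, 0.50 |

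The second row pools as (80+65+50)/3 = 65 and (20+35+50)/3 = 35. The third pools as (70+30+50)/3 = 50 and (30+70+50)/3 = 50. The pooled area is the same for rows one and two, and the same for rows three and four.

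**3. The same check with a continuous marker.** This is a simulation with 170 women per arm and 600 runs, using assumed log-odds slopes per standard deviation of the marker in the three arms.

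| Slopes by arm | Mean pooled ROC area | 2-df interaction test positive at 5% |
|---|---|---|
| 0.6, 0.6, 0.6 | 0.658 | 5% |
| 1.25, 0.6, 0 | 0.646 | 100% |
| 0.6, −0.6, 0 | 0.501 (area significant in 4% of runs) | 100% |

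The interaction test separates cases that the pooled ROC area does not.

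**4. What the trial could detect.** Compare two arms, with marker prevalence 50% (assumed), event rate 50% and two-sided alpha 0.05. The difference in risk differences has SE = √(4 × 0.25 / (n/2)) for n women per arm, and power = Φ(difference/SE − 1.96).

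| Women per arm with a sample | SE | 20 points | 30 points | 40 points |
|---|---|---|---|---|
| 170 | 0.1085 | 45% | 79% | 96% |
| 85 (assumed) | 0.1534 | 26% | 50% | 74% |

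A 20-point difference would need 2 × (1.96 + 1.282)²/0.20² ≈ 526 women per arm for 90% power, or about 393 for 80%.

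**The case against.** **The objective can be read more narrowly.** Section 2.2 speaks of the response to intervention, not to each intervention. Every woman receives an active treatment, so delivery before 37 weeks can be read as treatment failure, and a ROC area on the pre-intervention sample does address whether failure is predictable. This stands as one reading of Section 2.2 and the Professional Summary. It does not cover the purpose set out in Section 1.4, which is about one treatment succeeding over another.

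**The ROC plan serves real aims.** Section 2.4.2 (ix), and the comparison in Section 1.4 of women who deliver early with those who deliver at term, are prognostic, and Section 5 fits them. This stands in full. A reader might infer that the ROC analyses are wrong and should be replaced; the protocol does not support that.

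**Section 5 does not say that arms are pooled or that arm is left out of the regression, and a SAP may add the model.** This stands in part. The pooled areas above assume pooling, and areas compared between arms would go some way to answering the question. But the protocol does not leave the matter open. It sets out the biomarker analysis step by step, gives the regression another purpose, and plans subgroups only by risk factor.

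**Post-intervention samples.** A reader might infer that later samples are mixed with the pre-intervention sample. They are not: Section 5 analyses each time point separately. What remains is that the pre-intervention sample, the one the objective names, is given no role of its own.

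**The examples are extreme, and little depends on the objective.** Both stand. Between the two most different arms, the effect modifier in the table has a difference in risk differences of 60 points, and the opposite-effects marker 80 points. Nothing in the protocol suggests effects that large. The objective is secondary and exploratory, and no primary conclusion rests on it.

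**Conclusion.** The concern holds in a limited form. The objective in Section 2.2, read with Section 1.4, is about effect modification by pre-intervention marker status. The analysis stated in Section 5 is prognostic, does not use the allocated arm, and followed as written would leave that question unanswered. No stated number is wrong.

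The illustration shows what kind of failure this is, not how large it would be in this trial. Identical pooled ROC areas (0.65 and 0.65, or 0.50 and 0.50) can come from markers with entirely different implications for treatment choice. This rests on assumed rates, 50% marker prevalence and pooled arms. The between-treatment meaning of the objective comes from Section 1.4, not from Section 2.2 alone. The change is worth making because it is cheap and matches the analysis to a declared purpose. It does not bear on the primary comparison.

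**What to change.** In Section 5, add an analysis of the pre-intervention sample:

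- Fit a logistic model of delivery before 37 weeks on arm, marker and arm-by-marker interaction (2 df), in all randomised women who gave that sample.
- Report risk differences between arms with confidence intervals at each marker level, not only the interaction p-value.
- Report how many women in each arm gave the sample, since sampling follows open allocation.
- Keep the ROC, sensitivity, specificity and marker-combination analyses, labelled as a separate prognostic analysis.
- Restrict the interaction models to a short list of markers named in advance, or control for multiplicity, and label the results exploratory.

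**Cost.** No new data, visits or participants are needed: one further model per listed marker. The drawbacks are low power (about 45% for a 20-point difference in risk differences at 170 per arm, under the assumptions above) and multiplicity, since Section 4.3 foresees proteomic, microbiome and genomic methods. Optional sampling lowers the power further. So does the start of quantitative fetal fibronectin testing at 18 weeks for that marker, because women randomised and treated earlier will have no pre-intervention value. A null interaction result should therefore not be reported as evidence that response is the same at every marker level.

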## **6 Collection of outcome data**

Women will be followed up until postnatal discharge. Neonates will be followed up to discharge or 28 days (whichever is sooner). Prompts on the database will alert the research midwife/assistant when each trial participant reaches her delivery date. Birth registers and in-patient records will also be used to track hospital admissions and pregnancy outcomes. Outcome data (medical and economic) will be collected by review of obstetric handheld/electronic notes. The primary and secondary outcome data will be collected after discharge from neonatal care.

Measurement of outcome (medical and economic): will be collected via electronic patient records, and/or hand-held patient notes. If information is not available, e.g. if the delivery occurred elsewhere, the patient, patient's GP or other hospital will be contacted. Gestational age will be calculated using ultrasound estimated date of delivery predicted at the 12-15 week scan, or last menstrual delivery if miscarriage occurs prior to dating scan.

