#### **2.4.2 Secondary endpoints**

- i) Adverse perinatal outcome, defined as a composite outcome of death (antepartum/intrapartum stillbirths plus neonatal deaths prior to discharge from neonatal services) or one (or more) of intraventricular hemorrhage,

[figure not shown]

periventricular leukomalacia, hypoxic ischemic encephalopathy, necrotizing enterocolitis, bronchopulmonary dysplasia and sepsis.

- ii) Delivery <30 & 34 completed weeks' gestation.
- iii) Gestation at delivery.
- iv) Time between intervention and delivery.
- v) Requirement for Rescue Cerclage (bulging fetal membranes).
- vi) Other maternal and fetal outcomes: clinical course, therapies administered, maternal and fetal morbidity and mortality data until discharge or 28 days post-natal (whichever soonest).
- vii) Participant and clinician's perceptions of treatment: questionnaires with a selection of participants at 0-2 weeks post procedure. Questionnaires at one year are planned if funding is obtained.
- viii) Health costs at 28 days post-natal.
- ix) Biochemical end-points (on available samples): cervical swabs will be taken to determine the presence of cervicovaginal infection and concentrations of biomarkers of preterm birth, infection and inflammation. Saliva samples will be collected for salivary hormone levels, and blood samples taken for inflammatory markers and genetic analysis. Results will be correlated with maternal and fetal outcomes.

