### 3.6 Subsequent study visits

All participants will be seen in a follow up appointment, normally between 2 and 4 weeks post-intervention. Subsequently, all follow up visits will be at the discretion of the attending clinician. Each visit will be documented on the online database. A transvaginal ultrasound cervical length measurement should be performed, and results recorded on the trial database, at each visit. At each visit, information will be obtained on compliance, adverse events or pregnancy complications.

The final study visit will take place between 34+0 and 38+0-weeks' gestation. Patients randomised to progesterone will be asked to return all unused medication and empty blister packs, in order to collect compliance information. Patients randomised to pessary will return at 37 weeks for removal. Patients randomised to cerclage will be seen between 34 and 37 weeks, and an appointment made for removal in the appropriate clinical area (usually hospital birth centre). If delivery has occurred prior to this time, then study staff will contact the participants, to arrange a follow up visit and collection of unused medication. Other than the baseline post intervention visit and final study visit, all other trial visits will be times to routine clinic attendances according to local clinical protocols and clinician practice. Interim study data will therefore only be collected if the patient attends the appropriate department for routine purposes.

Note review will take place 28 days after delivery to capture to collect maternal, fetal and health economic data up until 28 days postnatal. A contact/visit with the participant is not required.

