### **3.7 Expected duration of the trial**

The end of the trial will be defined as 28 days post-delivery or discharge from hospital (whichever sooner) of the last recruited participant and infant. To achieve our projected numbers, we will involve at least three centres, each receiving referrals from satellite units, and will recruit over a 36 month period. Each site has a busy preterm birth surveillance clinic, with approximately 500 women screened each year. We anticipate that 30% of these (120/year) will develop a short cervix (< 25mm, based on our current EQUIPP database >20000 women at high risk of sPTB), and 50% (60) will be willing to be randomised in an RCT. Therefore over 36 months with recruitment from 3 centres, we would potentially be able to randomise 540 women with short cervixes.

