### 8.2.4 Treatment stopping rules

The trial may be prematurely discontinued by the Sponsor, Chief Investigator or Regulatory Authority on the basis of new safety information or for other reasons given by the DMEC/TSC regulatory authority or ethics committee concerned. If the trial is prematurely discontinued, active participants will be informed and no further participant data will be collected. The Competent Authority and Research Ethics Committee will be informed within 15 days of the early termination of the trial.

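### The neonatal composite has incompatible windows: deaths count to neonatal discharge in one section and to 28 days in another, and Section 6 gives two collection rules that disagree

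*Protocol*

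**What the plan says.** The neonatal composite appears in Section 2.2 under the primary objectives and in Section 2.4.2(i) as a secondary endpoint. Section 5 says it is not specifically powered for equivalence. Its time limits are:

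- **Section 2.2:** "assessed as a composite of perinatal death (within 28 days) and major morbidity".
- **Section 2.4.2(i):** "death (antepartum/intrapartum stillbirths plus neonatal deaths prior to discharge from neonatal services", with no limit in days. The morbidity components, which include "periventricular leukomalacia, hypoxic ischemic encephalopathy, necrotizing enterocolitis, bronchopulmonary dysplasia and sepsis", carry no time limit.
- **Section 6, follow-up:** "Neonates will be followed up to discharge or 28 days (whichever is sooner".
- **Section 6, collection:** "The primary and secondary outcome data will be collected after discharge from neonatal care".
- **Section 3.6:** "Note review will take place 28 days after delivery", to capture data up to that day.
- **Schedule of Visits:** the note review is at hospital discharge or 28 days, without saying whether the earlier or the later applies.

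Two other provisions limit what is collected. The section on expected duration of the trial sets the end at "28 days post-delivery or discharge from hospital (whichever sooner) of the last recruited participant and infant". Section 8.2.4 says that on premature discontinuation "active participants will be informed and no further participant data will be collected".

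**The concern.** A site cannot apply all these rules to the same infant. Whether a late death is an event depends on which section is read, and whether anyone looks for it depends on which sentence of Section 6 is followed. Sites could reasonably differ, and the endpoint would then mean different things at different centres.

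The infants concerned are those with long neonatal stays, mainly the earliest births, in whom a preterm-birth trial most needs complete neonatal data. The composite is also named in the primary objectives, so its definition matters although it is unpowered.

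The early-stopping rule has a different consequence. It would leave women who are still pregnant at the stop without the primary outcome.

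**Working it through.** **1. The neonatal window.** The protocol attaches no figure to this window, so there is none to reproduce. The check is to put three kinds of infant through each rule.

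| Infant | 2.4.2(i) | 2.2 | Section 6, follow-up | Section 6, collection | 3.6 |
|---|---|---|---|---|---|
| Dies in neonatal care on day 40 | event | not an event | outside | would be seen | outside |
| First listed morbidity after day 28, still in care | event (no limit) | no limit given for morbidity | outside | would be seen | outside |
| Discharged, then dies before day 28 | not an event | event | outside (discharge is sooner) | not settled | inside |

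No row is treated consistently. The third row shows that the mismatch also runs the other way, because the rule stops at whichever limit comes first.

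**2. Who could be affected.** Post-menstrual age at day 28 = gestation at birth + 4 weeks:

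- born at 24 weeks: 28 weeks
- born at 26 weeks: 30 weeks
- born at 28 weeks: 32 weeks
- born at 30 weeks: 34 weeks

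This shows which infants are plausibly still in care at day 28. It does not count events. The composite needs only one component, so an infant with an event by day 28 is classified correctly whatever happens later. Only first events after day 28 matter. The protocol gives neither lengths of stay nor late-event rates, so their number cannot be calculated.

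**3. Early stopping under Section 8.2.4.** Inputs from the protocol: 540 women over 36 months. Assumptions: even accrual, and a mean of 17 weeks from randomisation to delivery (range 14 to 21).

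- Accrual: 36 × 52/12 = 156 weeks; 540/156 = 3.46 women per week.
- Undelivered at a stop: 3.46 × 17 = 59 women (3.46 × 14 = 48; 3.46 × 21 = 73).
- Randomised by 12 months: 540/3 = 180. Without a primary outcome: 59/180 = 33% (27% to 40%).
- At 24 months, with 360 randomised: 59/360 = 16%.

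For the effect on the estimates, split the 17 weeks into an assumed 14 for preterm and 20 for term deliveries, alike in all arms. At 12 months the fractions with known outcome are 1 − 14/52 = 0.731 and 1 − 20/52 = 0.615.

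- True 50%: 0.5 × 0.731 / (0.5 × 0.731 + 0.5 × 0.615) = 54.3%.
- True 40%: 0.4 × 0.731 / (0.4 × 0.731 + 0.6 × 0.615) = 44.2%.
- True 60%: 0.6 × 0.731 / (0.6 × 0.731 + 0.4 × 0.615) = 64.0%.

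The risk difference between the last two reads 19.9 points instead of 20. The odds ratio stays at 2.25, because the two fractions cancel.

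**4. End of trial.** A woman randomised at 14+0 reaches 37 weeks 23 weeks later; one randomised at 23+6 does so about 13 weeks later. The last woman recruited need not be the last to deliver.

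**The case against.** The strongest reply is that Section 6 itself says outcome data are collected after neonatal discharge, so late events would be captured. This stands in part. A reader might infer from the 28-day rule that late events are lost, but the protocol does not say which sentence governs. Equally, the collection sentence fixes when data are gathered and does not expressly extend the window, so it does not remove the contradiction.

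Other stronger inferences are not supported either:

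- **That the cut-off favours equivalence.** The window is the same in every arm, the 20% margin is set for delivery before 37 weeks, and the composite is not powered for equivalence. Missed events lower the observed rates and could narrow absolute differences, but neither the size nor the effect on any conclusion can be shown.
- **That bed-days are wrongly cut off.** Section 2.4.2(viii) sets health costs at 28 days. That is a stated horizon, not an inconsistency.
- **That Section 8.2.4 contradicts the withdrawal section, which collects to delivery unless refused.** One covers an individual's withdrawal, the other discontinuation of the whole trial.
- **That early stopping would bias the comparison.** The shift from 50% to about 54% is in the pooled rate. The contrast between arms barely moves if delivery timing within the preterm and term groups is similar across arms.
- **That collection ceases for everyone when the last recruited woman finishes.** The protocol does not say so. Section 3.6 sets a note review after delivery for participants generally, and Section 6 describes database prompts for each participant.

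**Conclusion.** The conflict is real and should be fixed. Sections 2.2, 2.4.2(i), 3.6 and 6 and the visit schedule do not define one window for the composite, so whether a death or first morbidity counts can depend on the section read. If the 28-day limit governs, events after day 28 in infants still in neonatal care lie inside the endpoint and outside follow-up. Their number is unknown. The effect is confined to an unpowered endpoint that is listed as secondary but named in the primary objectives; delivery before 37 weeks does not depend on this window.

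Section 8.2.4 is a lesser, contingent weakness. Under the assumed accrual and time to delivery, a 12-month stop would leave roughly 30% of randomised women without a primary outcome. The cost is mainly precision, plus an upward shift in the pooled preterm rate. The end-of-trial definition is loose wording with no demonstrated loss of data.

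**What to change.** - State one window for the composite, covering death and each morbidity component, in Sections 2.2, 2.4.2(i), 3.6 and 6 and the Schedule of Visits: note review to discharge from neonatal services, or day 28 if later. Leave the 28-day horizon for costs as it is.
- At lower priority, amend Section 8.2.4 so that, after premature discontinuation, outcome and safety data continue to be taken from routine notes for all women already randomised, unless they refuse.
- Define the end of the trial, in the expected-duration section and in Section 17, by the last participant to complete follow-up.

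The cost is amendment wording, a later note review for infants still in hospital at day 28, and a later database lock while long stays finish. No extra participant visits are needed.
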